Few studies have focused on older people who call an EMS for a fall but are not conveyed or are rapidly discharged from ED after transportation [14]. They show that no intervention or specific care is scheduled after EMS intervention and the elderly who fall are often not treated in primary care practice [29, 30]. This population seems, however, to be particularly vulnerable with a high risk of mortality and institutionalisation. Therefore, they represent an interesting target for appropriate interventions [31, 32]. The RISING-DOM project has been designed as an answer to a critical request from our ED department to reduce resource utilisation for fall-related calls in the elderly and implementation of a fall-prevention strategy to decrease fall rates and related injuries.

In the RISING-DOM study, we intend to evaluate the subjects (70 years old and over) in their own environment by an experienced geriatric nurse whenever a fall triggers a call to the EMS (without hospitalisation or with an ED admission less than 24 h). A Personalised Intervention Care Plan (PIP) based on an initial comprehensive geriatric assessment is proposed, with targeted and prioritised actions in collaboration with the participant’s general practitioner (GP), hospital geriatrician and other health professionals if necessary. The PIP is based on the patient's desires and concerns and a maximum of three goals are established in order to increase participant's adherence.

The main purpose of the study is to assess the effect of this intervention on time to institutionalisation or death. Secondly, the impact of the PIP will be assessed regarding the number of institutionalisations or deaths, the number and time to first additional EMS call relating to a fall, the number and time to first unscheduled hospitalisation, the functional dependency level and the quality of life during follow up.

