### Data collection procedure and randomisation

During the phone call, prior to the enrolment of each participant, the investigator collects information related to the patient’s medical history, his/her current list of pharmacological and non-pharmacological treatment, his/her lifestyle and previous history of falls.

After study recruitment and collection of baseline data, each participant is randomly allocated (1:1) to either the intervention or control arm. Blocked randomisation with random block sizes will be performed. The randomisation will be stratified according to lifestyle (living alone versus living with one’s relatives) and the existence or not of a history of a fall in the previous 12 months and the site.

Data on outcomes (death, hospitalisations, institutionalisation and number of additional EMS calls relating to falls) are collected prospectively by the CRA at 6, 12, 18 and 24 months (M6, M12, M18 and M24 respectively) of the patient’s follow-up and then every six months until the end of the study for both groups. The Activities of Daily Living (ADL) [34] and quality of life (EQ-5D-5L) [36, 37] scales are collected by the CRA once a year at inclusion, 12 and 24 months of follow-up. The exhaustive list of the variables collected by the CRA during the RISING-DOM study for all patients (intervention and control group) is summarised in Table 3. For both groups, a log-book is given to the participants to prospectively collect the events occurring during the follow-up period such as falls, hospitalisations and other side effects with their date. This aims to help the CRA collect with precision the occurrence of events. This document is not accessed/collected by the study team and it works simply as a memory aid. Data collected during nurse home visits (six visits) and nurse phone calls (five phone calls) for the “intervention group” are listed in Table 4.

**Table 3 Tab3:** RISING-DOM data and timeline collection and for ‘intervention group’ and ‘usual-care control group

	CRA call	Investing call	CRA calls					
		Enrolment allocation	Baseline assessment	Follow-up assessment				
	-t1	t0	M0	M6	M12	M18	M24	^b^
Screening for eligibility	+	+						

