### Secondary outcomes

Secondary outcomes are collected at inclusion, 12 and 24 months follow-up and are as follows:

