**Unscheduled hospitalisation rate over 24 months**

**Time before occurrence of the first unscheduled hospitalisation**

**Death and institutionalisation rate over 24 months**

### Sample size

The 24-month event rate (institutionalisation or death before entering an institution) is estimated at 18% in the control arm based on available data in the literature [46]. A relative reduction of 30% is expected in the intervention arm at 24 months (Hazard Ratio = 0.679) with a two-sided test. 211 events should detect this Hazard Ratio (with a two-sided test Log-rank test) with a power of 80% and alpha risk of 0.05. With a study over 54 months, a uniform inclusion in the first 30 months and 10% of people lost to follow-up per year, it will be necessary to include 595 subjects per group to reach this number of events, thus 1,190 subjects in total.

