### Secondary outcomes analysis

The analysis of the secondary outcomes are conducted according to *(i)* a similar approach to that described for the analysis of the primary outcome for the criteria: time to the first additional EMS call relating to a fall and time to the first unscheduled hospitalisation *(ii)* the mean number of EMS calls relating to a fall, the mean number of unscheduled hospitalisations and the percentage of deceased or institutionalised subjects at 24 months will be compared between the two groups by generalised linear multi-variable models adjusted on the stratification and the potential confounding factors (age and AD, in particular) *(iii)* the comparison between the two groups of the level of the functional autonomy (ADL scale) and the quality of life ( EQ-5D-5L scale) at 24 months will be carried out by generalised multi-variable linear models adjusted to stratification and to the potential identified confounding factors (age) and the level of the score (ADL or EQ-5D-5L at inclusion) if appropriate.

Additional per protocol analysis will be conducted in the population of subjects who have complied with the protocol (in the intervention arm having accepted at least 80% of all visits and calls proposed during follow-up and for whom a PIP will have been proposed).

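### ADL and EQ-5D-5L are compared at month 24 only, which leaves the month-12 scores without a stated use, makes baseline adjustment conditional and gives no rule for deaths

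*Protocol article*

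**What the plan says.** Under Secondary outcomes analysis, item (iii), the comparison of ADL and EQ-5D-5L "at 24 months will be carried out by generalised multi-variable linear models adjusted to stratification". The other covariates named are age and "the level of the score (ADL or EQ-5D-5L at inclusion) if appropriate".

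The collection schedule is wider. Under Data collection procedure and randomisation, both "scales are collected by the CRA once a year at inclusion, 12 and 24 months of follow-up". Table 3 marks the same visits, and the Secondary outcomes section repeats them: "Secondary outcomes are collected at inclusion, 12 and 24 months follow-up".

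The objective is wider too. The last paragraph of the Background lists, among the effects to be assessed, "the functional dependency level and the quality of life during follow up". The Discussion likewise speaks of how functional autonomy evolves.

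On death, the Primary outcome analysis section plans sensitivity analyses for people who had died or been institutionalised by a missed follow-up. Secondary outcomes analysis extends that approach to the two time-to-event outcomes. Item (iii) has no counterpart.

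**The concern.** Three things are fixed in the text, and each could be fixed better at little cost.

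- **Month 12 is unused.** A participant scored at month 12 and lost afterwards gives nothing to a month-24 cross-sectional model. The analysis is also narrower than the objective it serves.
- **Baseline adjustment is conditional.** Whether the inclusion score enters the model should not be open to a later judgement, because that choice can change the estimate and its precision.
- **Death has no stated place.** Death is part of the primary composite, and the trial is powered on reducing that composite. A linear model for a month-24 score needs a score, and a participant who has died has none. If the intervention keeps some frail people alive, their low scores enter the intervention mean with no matching scores among controls.

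At stake are some precision and a foreseeable distortion in one direction: an intervention that works on survival could look slightly worse on function or quality of life.

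**Working it through.** **Inputs (Sample size section).** "The 24-month event rate (institutionalisation or death before entering an institution) is estimated at 18% in the control arm". "A relative reduction of 30% is expected in the intervention arm at 24 months (Hazard Ratio = 0.679) with a two-sided test". The section also gives 10% lost per year and 595 per arm.

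**The plan's own figures first.** Intervention 24-month rate: 0.18 × 0.70 = 0.126. HR = ln(0.874)/ln(0.82) = 0.679, as stated. Events by Schoenfeld: 4 × (1.960 + 0.842)² / (ln 0.679)² = 209.5, so 210 against the stated 211. The inputs are read correctly.

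**Participants lost between months 12 and 24.** With constant monthly hazards:

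- event hazard: −ln(0.82)/24 = 0.00827 (control), −ln(0.874)/24 = 0.00561 (intervention)
- loss hazard: −ln(0.90)/12 = 0.00878

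| | Control | Intervention |
|---|---|---|
| Event-free and followed at M12 | 0.815 | 0.841 |
| Event-free and followed at M24 | 0.82 × 0.81 = 0.664 | 0.874 × 0.81 = 0.708 |
| Leaving between M12 and M24 | 0.151 | 0.133 |
| Share of these that are losses | 0.00878/0.01705 = 0.515 | 0.00878/0.01439 = 0.610 |
| Lost, out of 595 | 46.2 | 48.4 |

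Total lost: 46.2 + 48.4 = 94.6, about 95. Ignoring events, the ceiling is (0.90 − 0.81) × 1,190 = 107.

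**Gain from month 12.** With monotone missing data, the variance of the month-24 mean is proportional to (1 − r²)/n24 + r²/n12, where r is the partial correlation of the month-12 and month-24 scores. The documents do not give r, so 0.4 to 0.8 is assumed.

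- Losses only (n12 = 0.90, n24 = 0.81): effective sample size up 1.6% to 6.8%.
- Losses plus deaths, with half the event hazard being death (control arm, 0.856 and 0.734): up 2.4% to 10.1%.

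The top of the range counts deaths as recoverable missing data, so the gain that is free of that assumption is about 2% to 7%.

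**Survivor bias with no true effect on the score.** Assume that score and frailty are standard normal with correlation ρ and that the frailest die first. If a proportion d has died, the survivors' mean score is ρ × φ(z_d)/(1 − d), where z_d is the d-quantile. The bias is the intervention value minus the control value.

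| Share of event hazard that is death | d, control | d, intervention | φ/(1 − d), control | φ/(1 − d), intervention | Bias, ρ = 0.3 | Bias, ρ = 0.7 |
|---|---|---|---|---|---|---|
| Half | 0.094 | 0.065 | 0.186 | 0.136 | −0.015 SD | −0.035 SD |
| All | 0.180 | 0.126 | 0.320 | 0.237 | −0.025 SD | −0.058 SD |

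For scale, the difference detectable with 80% power is 2.80 × √(2/n): 0.20 SD with 395 per arm and 0.18 SD with 466. A bias of 0.058 SD with 408 per arm would raise the two-sided type I error from 5% to about 13%. A bias of 0.015 SD with 440 per arm would raise it to about 5.6%.

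**The case against.** The strongest case against is that this is one condensed clause in a journal article. The Statistical methods section defers detail to an analysis plan that is not shown, and a single pre-specified time point at the end of a 24-month intervention is a legitimate choice. Both points are fair. A month-24 main contrast is not an error, and the handling of deaths and missing scores may be settled in that plan. They do not remove what is stated: the time point, the model family, the conditional baseline term, and an objective wider than the analysis.

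A reader might infer something stronger: that the plan restricts the comparison to those still measurable, ignores death, and is therefore biased. The documents do not say so. No analysis set is defined for this comparison, so that reading comes from silence.

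A reader might also take the 66% v 71% above as the shares with a month-24 score, and the 169 people leaving between the visits (0.151 × 595 + 0.133 × 595) as lost scores. That treats every primary event as a missing score. Institutionalised people can still be scored: Table 3 has no restriction to those at home, and the Outcomes section lets relatives, a legal representative or the GP supply outcome data.

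The same caution applies to a shift in mean ADL. Suppose the extra survivors score 2 points lower, an assumption with no source in the documents. The shift is then (0.708 − 0.664)/0.708 × 2 = 0.12 points if all events are deaths, but (0.757 − 0.733)/0.757 × 2 = 0.06 if half the event hazard is death and (0.783 − 0.771)/0.783 × 2 = 0.03 if a quarter is. Adjustment for age and baseline score would probably absorb part of it.

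Finally, a repeated-measures model does not itself handle death, because it treats scores after death as missing. That stands, and it shapes the fix.

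**Conclusion.** The point holds as a worthwhile improvement to a stated secondary analysis, not as a demonstrated bias. The month-24-only model is narrower than the protocol's own objective, leaves a full wave of collected scores without a use, and makes baseline adjustment optional. The precision at stake is modest: about 95 participants, and roughly 2% to 10% effective sample size if r lies between 0.4 and 0.8.

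The bias is a risk whose direction can be foreseen but whose size cannot be read from the documents. The figure of 0.015 to 0.058 SD rests on the hypothesised effect extending to deaths, on half or all of the event hazard being death, and on a frailty–score correlation of 0.3 to 0.7. If less of the hazard is death, the bias is smaller. It is well below the detectable difference of 0.18 to 0.20 SD. The primary outcome is unaffected.

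**What to change.** In the analysis plan, before the database freeze:

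1. Analyse ADL and EQ-5D-5L with a repeated-measures model on the month-12 and month-24 scores, including every randomised participant with either score. Always adjust for the baseline score, age and the stratification factors, and delete the condition attached to the baseline term. Keep the month-24 contrast as the main estimate.
2. Add one pre-specified supportive rank or ordinal analysis in which death ranks below every living state. Death should not be scored as ADL 0, because Table 1 uses that value for total dependency in a living person and the two would be tied.
3. State that the repeated-measures estimate is to be interpreted together with the supportive analysis, because it does not itself account for death.

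The cost is a little extra programming and one more reported analysis. No new data are needed.

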**Methods:**

Rising-Dom is a two-arm randomised (ratio 1:1), interventional, multi-centre and open study. Community-dwelling elderly people (≥ 70 years) who call an EMS for a fall at home are recruited. The intervention group receives home visits by a nurse with a comprehensive fall risk assessment and a personalised intervention care plan with a planned follow-up (six nurse home visits and five nurse phone calls). Subjects enrolled in the usual care-control group continue to receive their routine care for the prevention or treatment of diseases. Primary (time to institutionalisation or death) and secondary (unscheduled hospitalisations, additional EMS calls relating to falls, functional decline and quality of life) outcome data will be collected for both groups through five phone calls made by Clinical Research Associates (CRA) blind to the participants’ group during the follow-up period (24-months). Twelve hospital centres in the South-West of France are participating in the study as study sites. The inclusion period started in October 2019 and will end in March 2022. By the end of this period, 1,190 subjects are expected to be enrolled.

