***Summary data and monitoring***											
Monitoring of therapeutic changes					+		+		+		+
Compliance / difficulty of medication intake	+		+	+	+	+	+	+	+	+	+
Emerging of new events (pathologies, social, etc.)		+	+	+	+	+	+	+	+	+	+
PIP presentation and application mode		+	+	+	+	+	+	+	+	+	+
Adherence to recommendations		+	+	+	+	+	+	+	+	+	+
Primary care physician frequentation			+	+	+	+	+	+	+	+	+
Other specialist consultation			+	+	+	+	+	+	+	+	+

*GP* General Practitioner, *d* day, *M* month, *MMSE* Mini Mental State Examination, *Mini-GDS* Mini Geriatric Depression Scale, *SPPB* Short Physical Performance Battery, *ADL* Activities of daily living, *IADL* Instrumental Activities of Daily Living, *MNA* Mini Nutritional Assessment, *PIP* Personalised Intervention care Plan. Nurse visit 0 and 1 should be done within a maximum of 14 days and 30 days after enrolment. M2, M4, M6, M9, M12, M15, M18, M21 and M24 match months 2, 4, 6, 9, 12, 15, 18 and 24 respectively from the enrolment till the end of the follow-up period

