### Experimental design

An intervention includes three main actions: (*i*) CGA [35] and fall risk factor assessment, (*ii*) PIP to address potentially reversible and modifiable factors and (*iii*) patient follow-up by an experienced geriatric nurse over the 24-month follow-up period (Table 2).

(*i*) The CGA is performed during the first nurse visit at the participant’s home (V0) within a maximum of 14 days from the date of the EMS intervention. In addition, a fall record is performed to track potential risk factors (*e.g*. sensorial assessment, one-leg balance [43], Amsler grid [44], environmental hazards, etc.). Details on performed assessments and data collected throughout the nurse home visit are provided in Table 4.

(*ii*) A PIP is established throughout a Multidisciplinary Team Meeting (MDTM) within a maximum of 10 days following the first nurse visit. The geriatrician investigator, the nurse and the hospital pharmacist participate in this meeting to discuss the clinical and social status of the participant and suggest appropriate solutions regarding possible warning signs.

The PIP is proposed according to emphasis on preventing falls, standard geriatric recommendations [45], medical treatment adjustment and takes into account the patient's desires and concerns. It is discussed and approved beforehand by the participant’s GP and then given to the participant during the nurse visit at home within 10 days after the MDTM (V1). A maximum of three recommendations are proposed to the participants to maximise their adherence. For instance, prescription of physically adapted activities, attending of equilibrium and fall prevention workshops offered by the municipality, nutrition education, medication review carried out in a primary care setting, etc. The inclusion of the GP in the proposed intervention program should ensure patient adherence and compliance.

During the next four visits (V2, V3, V4, V5) every 6 months, the nurse re-evaluates the patient and ensures the effective application of the PIP or reports the possible blocking points. Relevant points are addressed after each visit to the participant’s GP. In addition, five nurse phone calls are scheduled at 2, 4, 9, 15 and 21 months (Fig. 1) in order to keep in touch with the participant and follow the PIP application.

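### The per-protocol set is defined by post-randomisation criteria stated for the intervention arm only, so its comparison is no longer randomised

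*Protocol article*

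**What the plan says.** The section Secondary outcomes analysis ends with: "Additional per protocol analysis will be conducted in the population of subjects who have complied with the protocol". A parenthesis then gives two criteria. The first is "in the intervention arm having accepted at least 80% of all visits and calls proposed during follow-up". The second limits the set further, to those "for whom a PIP will have been proposed". No criterion is given for controls, and no landmark, weighting or other handling of selection is attached to this set.

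The contacts in question are "six nurse home visits and five nurse phone calls". Table 2 gives them to the intervention group only; the study contacts listed for controls are mailed standard advice with a log-book and the outcome calls. On timing, the note to Table 4 says "Nurse visit 0 and 1 should be done within a maximum of 14 days and 30 days after enrolment". Experimental design adds "During the next four visits (V2, V3, V4, V5) every 6 months" and "five nurse phone calls are scheduled at 2, 4, 9, 15 and 21 months".

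Primary outcome analysis keeps intention to treat with a two-sided log-rank test.

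**The concern.** Acceptance of contacts and proposal of a PIP are both observed after randomisation, while institutionalisation and death are already accruing. Filtering one arm on them and not the other discards the balance that randomisation gave. There are three routes to bias:

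- **Adherer selection.** Those who decline contacts may differ in prognosis from those who accept. Their counterparts in the control arm cannot be identified and stay in.
- **Early events.** An intervention subject who dies or is institutionalised before a PIP is proposed drops out of the set; a comparable control does not.
- **An unclear denominator.** The rule does not say whether 80% is of contacts due while the person is still at home, or of the whole 24-month schedule. The second requires long event-free survival in one arm.

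At stake is how the result is read. An inconclusive intention-to-treat result could stand beside a favourable per-protocol hazard ratio, taken as the effect of following the programme. This comparison cannot estimate that effect.

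**Working it through.** **Inputs from Sample size:** 18% control event rate at 24 months; 30% relative reduction; two-sided alpha 0.05; 80% power; 595 per arm; 10% loss per year; 30 months of accrual within 54 months.

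**The plan's own figures.** HR = ln(1 − 0.126)/ln(1 − 0.18) = 0.1347/0.1985 = 0.679, as stated. Events (Schoenfeld) = 4 × (1.96 + 0.84)²/(ln 0.679)² = 209.5, so 210; Freedman gives 215. The stated 211 is reproduced closely. No figure is stated for the per-protocol set.

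**Early events.** Control hazard = −ln(0.82)/24 = 0.00827 per month. Expected events in the first 30 days = 595 × [1 − exp(−0.00827 × 30/30.44)] = 595 × 0.0081 = 4.8. With no true effect this holds in each arm; it is dropped from one and kept in the other. Adding the stage limits in Experimental design instead (14 + 10 + 10 = 34 days) gives 5.5.

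**Adherer selection.** Let p be the share of intervention subjects excluded for low acceptance and k their event hazard relative to adherers. With no true effect the control arm has average hazard h(1 − p + pk) and the retained intervention arm has h, so the apparent HR is about 1/(1 − p + pk). The documents give neither p nor k, so these are assumptions:

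| p | k | Null HR |
|---|---|---|
| 15% | 1.5 | 1/1.075 = 0.93 |
| 25% | 2.0 | 1/1.25 = 0.80 |
| 25% | 0.7 (refusers fitter) | 1/0.925 = 1.08 |

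**Denominator.** 80% of 11 is 8.8, so 9 contacts are needed. In order they are V0, V1, M2, M4, M6, M9, M12, M15, M18, and the ninth falls at M18. On a full-schedule denominator, no intervention subject with an event before about 18 months can qualify. Control risk to 18 months is 1 − exp(−0.00827 × 18) = 13.8%. A subject already event-free at 18 months has a risk of only 1 − exp(−0.00827 × 6) = 4.8% by month 24, against 18% in controls.

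**Simulation with no true effect.** 595 per arm, exponential events and loss, follow-up uniform over 24 to 54 months, 1,000 replicates, contacts assumed to stop at event or loss, filter on the intervention arm only:

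| Analysis set | HR | Log-rank rejection |
|---|---|---|
| Intention to treat | 1.00 | 5% |
| Contacts due while at home, all accepted | 0.97 | about 6% |
| Same, mean acceptance 90%, lower in frailer subjects (frailty variance 0.5 to 1.0) | 0.82 to 0.73 | 33% to 61% |
| 9 of all 11 contacts | 0.48 | 100% |

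In the last row 55% of intervention events are removed. The third row rests on assumed acceptance and frailty, and not all of it is frailty. An 80% rule on few contacts is harder to meet: at 90% acceptance, four of four has probability 0.9⁴ = 0.66, while at least nine of eleven has 0.91. A person with an early event is therefore more likely to fail the ratio even when acceptance is unrelated to frailty.

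**The case against.** The set is first described for both arms as those who complied, and the parenthesis may give only the intervention-specific part. A detailed analysis plan, not shown, could add criteria for controls such as eligibility. A reader might infer that every control is retained; the article does not say so. This stands, but controls have no nurse contacts or PIP, so no control criterion could mirror the stated ones.

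A reader might also infer that the retained intervention subjects are markedly longer survivors. The text counts contacts proposed during follow-up, and contacts are hardly proposed after death. On that reading, with full acceptance, forced survival is only about 30 days and the null HR is 0.97. The PIP must also only be proposed, not received. The large immortal-time effect belongs to the full-schedule denominator, which the wording leaves open but does not state.

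The direction is not proven. Refusers could be fitter people who see no need, and home, telephone or video contact limits absences caused by frailty. The planned models adjust for age, ADL and stratification factors and may remove part of any frailty selection. The hazard ratios above are unadjusted.

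Finally, the analysis is additional, it sits under the secondary outcomes, and no decision is tied to it. The text does not say whether the primary outcome is re-analysed in this set. All of this limits the weight of the point. It does not restore a randomised comparison.

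**Conclusion.** The point holds as a moderate one. The stated rule selects on post-randomisation behaviour in one arm, so the comparison is no longer randomised. The size of the bias depends on unknowns:

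- About 5 of 595 intervention subjects are lost to the PIP condition under the null, a small effect.
- Adherer selection gives a null HR of about 0.93 to 0.80 if refusers are frailer, on assumed p and k and before adjustment, and above 1 if they are fitter.
- A full-schedule denominator gives about 0.48.

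Two stronger readings are not supported. One is that the artefact matches the whole design effect of 0.679: the formula reaches 0.69 only with p = 30% and k = 2.5, a pair for which the documents give no basis. The other is that the trial's main conclusion is at risk: the primary intention-to-treat log-rank test is untouched.

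**What to change.** Replace the per-protocol comparison, or accompany it, with a complier-average effect using randomisation as the instrument. This is the intention-to-treat difference in 24-month event-free probability divided by the proportion of the intervention arm exposed to the programme, with a bootstrap confidence interval. All randomised subjects in both arms are kept.

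Define exposure early, for example first nurse visit done or PIP proposed, and not by the 80% threshold. Someone who accepts 8 of 11 contacts (73%) may have had the geriatric assessment, the PIP and months of follow-up. Counting that person as untreated breaks the exclusion restriction and inflates the estimate. State that restriction: allocation has no effect on people who are not exposed. As an illustration, the planned difference of 18% − 12.6% = 5.4 points with an assumed 85% exposed gives 5.4/0.85 = 6.4 points.

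If the per-protocol set is still shown:

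- label it descriptive;
- count only contacts due before the event or censoring;
- start both arms at a common landmark, with adherence counted up to it;
- adjust for baseline age, ADL and the stratification factors;
- state that adherer selection remains, because the landmark removes only the immortal time.

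The cost is analysis-plan wording and one extra estimator. Statistical methods allows changes before database freeze with Scientific Council approval. The downsides are a wider confidence interval than the naive comparison and reliance on the exclusion restriction.
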